## Abstract

**Background:**

Conventional image-guided radiotherapy (IGRT) typically relies on a computed tomography (CT)-based treatment planning process (planning CT, pCT) performed prior to the start of treatment. During this process, a patient-specific treatment plan is generated, which is then delivered to the patient with a linear accelerator on a daily basis, usually with image guidance to compensate for variations in patient setup. However, daily interfractional anatomical variations in target position, shape, and volume, as well as in surrounding organs at risk (OARs), can only be addressed indirectly by adding safety margins, resulting in larger irradiated volumes and potentially increased toxicity. Online adaptive radiotherapy (oART) is a promising and innovative technique to reduce such margins and, consequently, treatment-related toxicity. It uses daily imaging to generate a “plan of the day” that is aligned with the current patient anatomy, often supported by artificial intelligence (AI), while the patient remains on the treatment couch. Through daily image-guided re-optimization of the radiation treatment (RT) plan on the anatomy of the day, target coverage may also be improved. This approach is particularly attractive in the pelvic region, where high interfractional anatomical variability, for example due to peristalsis or changes in bladder and rectal filling, is frequently observed.

**Methods:**

This prospective registry-based cohort study will include patients with pelvic or thoracic tumors with an indication for RT treated with IGRT or oART using the Varian Ethos™ system. The primary endpoint is defined as a 10% reduction in the rate of acute RT related toxicity (≥Common Terminology Criteria for Adverse Events (CTCAE) II°, v5.0) using oART. Secondary endpoints encompass clinical outcomes including late toxicities, tumor control rates, and patient-reported outcomes (PROs), as well as technical factors such as target volume, coverage, dose to OARs and anatomical variability score. While the cohort study compares IGRT versus oART for primary and secondary clinical endpoints, it also evaluates the real oART scenario against two hypothetical control scenarios for technical endpoints.

**Discussion:**

The introduction of oART promises a reduction in toxicities and improved target volume coverage, potentially resulting in enhanced tumor control rates. It is poised to be a pioneering technology in the field of radiation oncology. Given the absence of a direct comparison between IGRT and oART thus far, the prospective registry-based cohort study PRoART aims to address this gap.

**Trial registration:**

Clinical trial number NCT06185062, Clinicaltrials.gov. Registered 12/14/2023. Last update 07/29/2026.

## Background

Approximately 500 000 patients in Germany are diagnosed with malignant neoplasms annually [1]. Radiation oncology is a pillar of oncologic treatment, alongside surgical and pharmacological tumor therapy for many patients. About half of oncology patients receive radiation therapy (RT), typically delivered using medical linear accelerators [2]. A radiation treatment plan is developed based on an initial computed tomography (CT; planning CT, pCT) scan taken before therapy, balancing the dose to the target volume while minimizing exposure to surrounding healthy tissue (organs at risk, OARs). This plan is administered in each treatment session, usually with X-ray-based imaging on the linear accelerator (2D X-ray or 3D Cone-Beam CT, CBCT), followed by positional correction via automated movement of the treatment couch, a process known as Image-Guided Radiotherapy (IGRT). This method only corrects for translational and rotational setup errors by best fitting the static, pre-planned dose distribution of the treatment plan to the daily anatomy, which often requires compromise if organs have shifted in a relevant manner. In contrast, Online Adaptive Radiotherapy (oART) is a procedure in which the radiation plan and corresponding dose distribution are re-optimized on a daily basis to better match the patient’s current anatomy and morphology. Fischer et al. analyzed the impact of oART on prostate bed treatment in a retrospective study of 198 fractions from six patients receiving IMRT, demonstrating a significant improvement in target coverage (D98%) and decreased variability in dose delivery after adaptation [3]. However, to date, only limited published data are available on the clinical benefit of oART, highlighting the need for further prospective studies. A CBCT scan from the linear accelerator before each session provides the basis for this adapted plan, using the initial “old” plan as a reference. This method employs artificial intelligence (AI) to account for both translation and rotation errors, as well as daily interfractional anatomical variations in organ position and size. AI and machine learning are for the first time being used effectively in radiation oncology to reduce treatment planning processes that previously took several days to just minutes. Despite the use of AI, oART requires significant resources in personnel and time compared to IGRT [4]. However, this extra effort is justified by the potential clinical benefits in improved treatment quality. This strategy is particularly promising in the pelvic region due to significant interfractional anatomical variability, such as peristalsis and volume changes in the bladder and rectum.

In recent decades, technological advancements and the implementation of new techniques have significantly reduced the side effects associated with RT. For prostate cancer, Intensity-Modulated Radiotherapy (IMRT) and rotational techniques deliver higher doses to the prostate/prostatic fossa while minimizing exposure to OARs. A prospective, randomized phase III trial “RTOG 0126” showed that IMRT reduced late gastrointestinal (GI) toxicity by 26% compared to 3D-conformal radiotherapy (3D-CRT) [5]. A meta-analysis of 23 studies confirmed that IMRT significantly reduces the incidence of acute GI toxicity by 41% [6]. In other pelvic tumor entities, anatomical variability impacts RT as well. Studies show that oART can significantly improve target volume coverage and reduce OAR dose exposure in primary bladder cancer treatment, potentially lowering acute GI toxicity [7]. Improved sparing of OARs has been shown to reduce therapy-related side effects, as evidenced by studies comparing IMRT with 3D-CRT [8]. In gynecological cancers, oART promises improved target coverage by considering uterine configurations and bladder volumes. Adjuvant radiochemotherapy (RChT) in cervical cancer, delivered using modern IMRT, has shown significantly lower treatment associated toxicity without compromising oncologic outcomes. The randomized phase III trial “PARCER” revealed that, following a median follow-up of 46 months, the cumulative incidence of late grade ≥ II GI toxicity was reduced by half in the IMRT-arm, standing at 21.1% versus 42.2% in 3D-CRT (*p* < 0.001). The cumulative incidence of any late toxicity amounted to 28.1% with IMRT, compared to 48.8% (*p* < 0.001) observed with 3D-CRT [9]. In contrast to pelvic tumors, which often show marked day-to-day anatomical variations due to changing organ volumes, thoracic tumors, such as non-small-cell lung cancer (NSCLC) and small-cell lung cancer (SCLC), exhibit therapy-associated changes like re-opening of atelectasis, resulting in significant anatomical shifts during treatment. Current management involves periodic CT scans and “offline” re-planning [10]. Initial positron-emission tomography (PET)- based planning [11] and additional oART could minimize target volumes and protect healthy tissues. Radiation pneumonitis is a feared side effect, occurring in around 29% of patients after R(Ch)T for NSCLC [12] but recent phase III studies with improved techniques like IMRT have significantly reduced this rate to 0–7.5% [11, 13, 14]. Precision techniques such as IMRT and oART lower toxicity and allow for potential adjuvant immunotherapy in suitable cases [10]. Despite these advancements, reducing acute and chronic side effects remains crucial for patients’ quality of life and treatment decisions.

## Methods and design

### Study design

This clinical study is a prospective and retrospective observational registry-based study that systematically collects data on oART and conventional IGRT in routine clinical practice. Participants are not randomized, nor are they blinded. Three registries will be established due to fundamental differences in diagnosis and treatment among the entities 1) prostate/prostate bed irradiation, 2) pelvic tumors excluding the prostate and 3) thoracic tumors. The primary endpoint is a 10% reduction in RT-associated acute toxicity (Common Terminology Criteria for Adverse Events (CTCAE) v5.0 ≥ Grade II) in the oART cohort compared to the IGRT cohort.

The study comprises two complementary parts: a prospective clinical cohort of patients treated with either oART or IGRT, and virtual sub-cohort in which, for each fraction in the oART arm, the adapted plan is systematically compared with two automatically generated non-adapted reference plans to analyze physical and technical endpoints.

Data collection will be multicentric and will initially take place over six years. Interim analyses are scheduled after 141 patients per cohort, for each registry. The study is endorsed by the working group for Adaptive Radiotherapy of the German Society for Radiation Oncology (DEGRO) and the Radiation Oncology working group (ARO) of the German Cancer Society (DKG). Enrollment of additional centers will be possible during the period of data collection.

**Fig. 1 Fig1:**
[figure not shown]
Flow chart of the clinical cohort; legend: IGRT = image guided Radiotherapy; oART = online adaptive radiotherapy

An evaluation and testing of the Ethos™ linear accelerator and AI system have already been performed by Varian (Varian Adaptive Intelligence™). The linear accelerator and AI system are certified by the CE (Conformité Européenne) and FDA (Food and Drug Administration, United States).

### Primary endpoint

The primary endpoint is defined as a 10% absolute reduction in the incidence of acute toxicity of grade ≥ II according to CTCAE v5.0, occurring during RT and within twelve weeks after completion of treatment. In addition, we will distinguish between grade II toxicity and toxicity of grade ≥ III. The primary endpoint will be assessed in the clinical cohort (Table 1).

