## Study procedures

The study design follows the typical clinical workflow and execution of a RT course. Patients are included in the PRoART study after being evaluated in the outpatient clinic, informed about the treatment and study process, and providing written informed consent. Initially, baseline data on the tumor entity and its specific characteristics, such as tumor stage, histology, biomarkers, diagnostics, and previous treatment, are collected. Baseline HRQoL is also measured. Study participants are not formally randomized or blinded. The decision to provide the patient with oART on the Ethos™ system is made by the medical team in routine clinical care, primarily based on current capacity for adaptive treatments and patient suitability (for example, tolerance of the relatively long treatment duration and time spent lying on the treatment couch). If no capacity is available at the time of consultation, or if the patient is unsuitable due to their physical condition or comorbidities, the patient is assigned to conventional IGRT.

Both cohorts receive an initial pCT before therapy, on which the corresponding treatment plan is generated, a planning process that may take several days. Both medical and technical personnel are involved, and an individualized treatment plan is generated for each patient through interdisciplinary consultation. This plan is usually a compromise between achieving full target coverage (tumor region ± affected lymph nodes) and minimizing exposure to OARs.

During RT, which is typically administered daily on weekdays over several weeks (depending on the tumor type), a weekly patient visit takes place. Along with assessing acute toxicity, guideline-based supportive therapy can be initiated to alleviate symptoms, if necessary. At the final treatment session, patient satisfaction will be evaluated alongside quality of life in both groups. This assessment aims to determine whether the longer treatment duration and time spent on the treatment couch during oART affect patient satisfaction.

The patients then proceed with guideline-based follow-up care with their specialized oncologists. RT follow-up to monitor long-term toxicity and tumor status is conducted quarterly for the first two years after treatment ends, and then every six months from the third to the fifth year post-treatment.

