**Fig. 4 Fig4:**
[figure not shown]
Schedule of assessments of PRoART

The following validated questionnaires will be used to evaluate clinical endpoints:CTCAE v.5.0 to assess acute and late treatment-related toxicity [15]PRO-CTCAE® v1.0 to assess HRQoL [16]EORTC QLQ-C30 v3.0 to assess HRQoL [17]Epic-26 (Expanded Prostate Cancer Index Composite with 26 items) and IPSS (International Prostate Symptom Score) to assess HRQoL in prostate cancer patients [18, 19]PSQ-18 (Patient Satisfaction Questionnaire Short Form) to measure patient satisfaction [20]

In addition to the prospectively collected data, the registry will also include data from oART treatments conducted prior to study initiation. These will be collected retrospectively after informing the patients and obtaining their written consent to participate in the study. Retrospective data will be clearly marked and will be analyzed separately to maintain transparency and comparability within the ongoing registry.

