## Statistical analysis

The primary endpoint is defined as an absolute reduction in the incidence of acute CTCAE v5.0 grade ≥ II toxicity from 15% to 5% in the oART cohort compared with the IGRT cohort, corresponding to a 10 percentage point absolute reduction. To achieve a power of 80% with a two sided alpha level of 5%, an initial cohort size of *n* = 141 patients per arm (*n* = 282 in total) is required to detect a statistically significant difference (*p* ≤ 0.05) between the oART and IGRT cohorts. The sample size calculation was performed using a chi-squared test for two independent proportions in nQuery (Version 9.5.2). Once *n* = 141 patients per cohort and registry have been reached, an interim analysis of the primary endpoint will be conducted. The sample size calculation was performed in collaboration with the Institute of Medical Statistics at the University Medical Center Goettingen.

For the primary endpoint of acute toxicity and the secondary endpoint of late toxicity, occurrence per patient will be statistically analyzed using general linear models and logistic regression, incorporating baseline covariates like chemo-/immune-/hormone deprivation therapy (yes/no), tumor size, TNM staging/grading/risk scores, and lymph node radiation (yes/no). Proportions will be presented with a 95% confidence interval.

Tumor control and survival rates will be compared between the cohorts using Cox regression, adjusted for covariates, and reported as hazard ratios with 95% confidence intervals.

HRQoL, patient satisfaction, technical endpoints, and other continuous variables will be modeled using mixed linear models to identify marginal group effects, adjusting for relevant baseline covariates such as performance status.

As a registry-based study, patient data will continue to be collected even after the initial analysis of the primary endpoint.

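### The covariates named for the primary acute-toxicity model omit fitness and baseline symptoms, although fitness helps decide who receives IGRT

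*Protocol article*

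**What the plan says.** **Endpoint.** The protocol article, Primary endpoint, takes the incidence of acute CTCAE v5.0 grade ≥ II toxicity "occurring during RT and within twelve weeks after completion of treatment". Elsewhere the toxicity is tied to radiotherapy. The abstract has a "10% reduction in the rate of acute RT related toxicity", Study design says "The primary endpoint is a 10% reduction in RT-associated acute toxicity", and the questionnaire list under Study procedures uses CTCAE "to assess acute and late treatment-related toxicity". No passage says how relatedness is judged or how a symptom already at grade ≥ II before RT is treated.

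**Allocation.** Study design says there is neither randomisation nor blinding. Slot availability is given as the main determinant of treatment, but Study procedures adds a second route: "if the patient is unsuitable due to their physical condition or comorbidities, the patient is assigned to conventional IGRT". The limitations paragraph of the Discussion says instead that assignment takes place only among patients clinically eligible for both techniques.

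**Model.** For acute and late toxicity, Statistical analysis plans general linear models and logistic regression, "incorporating baseline covariates like chemo-/immune-/hormone deprivation therapy (yes/no), tumor size, TNM staging/grading/risk scores, and lymph node radiation (yes/no". Two paragraphs later it names performance status as an example covariate, for the models of HRQoL, satisfaction, technical endpoints and other continuous variables.

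**Baseline data.** Study procedures states "Baseline HRQoL is also measured" and that patient-reported baseline data are taken once before RT. The HRQoL instruments listed are QLQ-C30 and, for prostate patients, EPIC-26 and IPSS; PRO-CTCAE is also listed.

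**The concern.** In a non-randomised comparison, the covariates that matter most are those that influence both allocation and outcome. The protocol identifies such a factor itself: physical condition and comorbidity, described in terms of tolerating long sessions on the couch. Urinary urgency, bowel symptoms or dyspnoea could plausibly limit that tolerance, and the same symptoms are graded as acute toxicity from the first weekly visit by staff who know the technique. The variables named for the primary model (systemic therapy, tumour size, stage, grade or risk score, nodal irradiation) do not describe the patient's condition. The one covariate that does, performance status, is attached to other endpoints.

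If less fit or more symptomatic patients gather in the IGRT cohort, IGRT will show more grade ≥ II events for reasons unrelated to technique. Part or all of a reported oART benefit could then be an allocation effect.

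**Working it through.** **1. The plan's own figure.** Inputs from Statistical analysis: 15% against 5%, two-sided alpha 5%, power 80%, chi-squared test. With the pooled variance under the null and mean rate 0.10:

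n = [1.96·√(2·0.10·0.90) + 0.8416·√(0.15·0.85 + 0.05·0.95)]² / 0.10² = (0.8316 + 0.3521)² / 0.01 ≈ 140.1, hence 141 per arm.

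This agrees with the stated 141; power at 141 is 80.3%. The sizing has no arithmetic error.

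**2. Covariates against the allocation route.**

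| Factor | Affects allocation? | Named for the toxicity model? |
|---|---|---|
| Systemic therapy, tumour size, stage/grade/risk, nodal RT | Not stated | Yes |
| Physical condition, comorbidity | Yes (Study procedures) | No; performance status is named for the continuous outcomes only |
| Baseline symptoms | Plausibly, through couch tolerance | No |

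**3. Size of the possible bias, for illustration.** Let q be the new-toxicity rate, equal in both arms (no true effect), and let b be the share of patients with a baseline symptom that is counted as an event. Independence of the two is assumed. The event rate is b + (1 − b)·q, so the spurious difference is (b_IGRT − b_oART)·(1 − q). I take q = 15% from the plan. Both values of b are assumptions.

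- b = 20% against 10%: rates 0.20 + 0.80·0.15 = 32.0% and 0.10 + 0.90·0.15 = 23.5%. The difference is 0.10·0.85 = 8.5 points. With 141 per arm, the unadjusted chi-squared test favours oART in about 36% of trials, against a nominal 2.5% in that direction.
- b = 10% against 5%: rates 23.5% and 19.25%, difference 4.25 points, rejection about 14%.

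If a baseline symptom or poor fitness is not itself counted but raises the risk of a counted event from q to some r below 1, the difference becomes (b_IGRT − b_oART)·(r − q). The bias is then smaller, but it does not vanish.

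**4. Dilution, only if prevalent symptoms were counted.** With equal b in both arms added to new-toxicity rates of 15% and 5%:

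| Assumed b | IGRT | oART | Difference (points) | Power at 141 per arm |
|---|---|---|---|---|
| 0% | 15% | 5% | 10 | 80% |
| 5% | 19.25% | 9.75% | 9.5 | 62% |
| 10% | 23.5% | 14.5% | 9.0 | 49% |
| 20% | 32% | 24% | 8.0 | 32% |

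**The case against.** A reader might infer that symptoms present before RT are counted and that the treatment difference is therefore diluted. The documents do not support that. The endpoint is an incidence, and three other places call the toxicity related to radiotherapy; a symptom that precedes the first fraction is not. The planning rates point the same way: if 5% of oART patients carried a counted baseline symptom, the planned 5% total would leave a new-toxicity rate of (0.05 − 0.05)/0.95 = 0. The dilution table therefore depends on a reading that the text does not adopt. Detailed scoring rules may also sit in the full protocol or case report form, and the schedule in Fig. 4 is not shown.

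It is also fair that the covariate list is introduced as examples, and that the Discussion promises baseline data collection, statistical adjustment and sensitivity analyses. Slot availability is said to be the main driver of allocation, and the Discussion's eligibility statement, if it governs, would weaken the fitness route. The 36% comes from an unadjusted test, whereas the planned analysis is adjusted.

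What remains is narrower. The general promise names no variable, and the examples omit the one factor that Study procedures makes a reason for allocation. Adjusting for tumour and treatment variables helps only so far as they happen to correlate with fitness. The eligibility statement cannot be relied on as protection while Study procedures says otherwise.

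**Conclusion.** The point holds for the covariates. As written, the primary toxicity model names no measure of fitness or baseline symptoms, while fitness is a stated reason for receiving IGRT. If these factors differ by arm, the named covariates would not remove the resulting bias, which would probably favour oART. Its size cannot be known from the documents. The 8.5 points with about 36% rejection, and the 4.25 points with about 14%, rest on assumed prevalences, on those symptoms being counted, and on no adjustment for anything correlated with them.

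The endpoint definition calls for clarification rather than correction: it does not say how pre-existing symptoms are separated from radiotherapy-related toxicity, and in an unblinded study this leaves the call to the rater. Dilution is conditional on counting them. Because dilution and confounding can act in opposite directions, the net effect is not determined. The change is worth making: it costs little, and a pre-RT grade that was not recorded is hard to recover later, with enrolment open since January 2024.

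**What to change.** 1. In Statistical analysis, pre-specify performance status and one baseline symptom score as covariates in the primary logistic model: IPSS or EPIC-26 in the prostate registry, and baseline QLQ-C30 or other baseline patient-reported data in the pelvic and thoracic registries.
2. In Primary endpoint, state that an event counts only if it is new or worse than the pre-RT grade and reaches grade ≥ II. Record the pre-RT CTCAE grade at the existing outpatient evaluation, if the schedule does not already provide for it.
3. Reconcile Study procedures with the Discussion on whether patients unsuitable for oART enter the IGRT cohort.

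**Cost.** One sentence in the endpoint definition, one or two more model terms, and baseline questionnaire data that the study already plans to collect. The event count may fall slightly. At the planning rates a registry expects about 0.15·141 + 0.05·141 ≈ 28 events, so each added covariate should enter as a single term.
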